## Summary of the main multicentre study project

|                                |                                                                                                                                                                                                                                                                                                                                                                                    |
|--------------------------------|------------------------------------------------------------------------------------------------------------------------------------------------------------------------------------------------------------------------------------------------------------------------------------------------------------------------------------------------------------------------------------|
| Title                   | A Randomised Controlled Trial Of Early Insulin Therapy In Very Low Birth Weight Infants                                                                                                                                                                                                                                                                                            |
| Principal Investigator  | [name]                                                                                                                                                                                                                                                                                                                                                             |
| Study Sites             | Addenbrooke's Hospital, Cambridge, UK
New Royal Infirmary of Edinburgh, Edinburgh, UK
Luton and Dunstable Hospital, Luton, UK
Leeds General Infirmary, Leeds, UK
Kindergeneeskunde, U.Z., Leuven, Belgium
Hospital Universitari, Sant Joan de Deu, Barcelona, Spain
VU University Medical Center, Amsterdam, The Netherlands
ZOL Campus St Jan, Genk, Belgium |
| Name of Product         | Insulin aspart with variable rates
20% dextrose support                                                                                                                                                                                                                                                                                                                         |
| Dose                    | 0.05 units/kg/hour                                                                                                                                                                                                                                                                                                                                                                 |
| Route of administration | Continuous intravenous infusion in the first week of life                                                                                                                                                                                                                                                                                                                          |
| Study objective         | To evaluate the effect of early fixed dose insulin on mortality in very low birth weight babies                                                                                                                                                                                                                                                                                    |
| Study Design            | Randomised controlled study.                                                                                                                                                                                                                                                                                                                                                       |
| Study Population        | Infants with birth weight <1500g and recruited within 24 hours of birth                                                                                                                                                                                                                                                                                                            |

|                                   |                                                                                   |
|-----------------------------------|-----------------------------------------------------------------------------------|
| Number of Patients         | 500                                                                               |
| Multicentre                | Yes                                                                               |
| Number of Centres          | 8 (4 UK)                                                                          |
| Allocation of Treatment    | Randomisation to treatment or control if all inclusion/exclusion criteria are met |
| Primary Efficacy variable  | Mortality on or before expected date of delivery (EDD)                            |
| Clinical Efficacy variable | Improved glucose control (blood glucose 4-8 mmol/l)                               |
| Safety Variables           | Glucose monitoring – prevalence of hypoglycaemia                                  |
| Adverse Events             | To be recorded by nursing staff on adverse event form                             |

## Summary of the local amendment

|                                  |                                                                                                                                                                                                                      |
|----------------------------------|----------------------------------------------------------------------------------------------------------------------------------------------------------------------------------------------------------------------|
| Title                     | A Randomised Controlled Trial Of Early Insulin Therapy In Very Low Birth Weight Infants; influences on growth, body composition, neuro-motor development and neuro-endocrine axes during infancy and early childhood |
| Principal Investigator    | [name] [name]                                                                                                                                                                                       |
| Study Site                | VU University Medical Center, Amsterdam, The Netherlands                                                                                                                                                             |
| Name of Product           | Insulin aspart with variable rates
20% dextrose support                                                                                                                                                           |
| Dose                      | 0.05 units /kg/hour                                                                                                                                                                                                  |
| Route of administration   | Continuous intravenous infusion in the first week of life                                                                                                                                                            |
| Study objective           | To evaluate the effect of early fixed dose insulin on growth, body composition, neuro-motor development, and neuro-endocrine axes during the first years of life                                                     |
| Study Design              | Randomised controlled study.                                                                                                                                                                                         |
| Study Population          | Infants with birth weight <1500g and recruited within 24 hours of birth                                                                                                                                              |
| Number of Patients        | 60                                                                                                                                                                                                                   |
| Multicentre               | No                                                                                                                                                                                                                   |
| Allocation of Treatment   | Randomisation to treatment or control if all inclusion/exclusion criteria are met                                                                                                                                    |
| Primary Efficacy variable | Improved growth, body composition, neuro-motor development and function of the neuro-endocrine axes                                                                                                                  |

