## **Questions:**

### Primary questions:

1. Does insulin replacement in preterm infants during the first week of life improve insulin sensitivity, early postnatal growth, catch up growth and body composition during the first years of life?
2. Does insulin replacement during the first week of life have implications for the development and function of the HPA and HPG axis?
3. Does insulin replacement during the first week of life have implications for the neuro-motor development during infancy and early childhood?

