### Objectives

#### Primary:

1. Growth and catch up growth and body composition during the first two years corrected age

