#### Secondary

1. Insulin sensitivity at the age of 6 months and 2 years
2. Adrenal function at the age of 6 months and 2 years
3. Development of the HPG axis postnatally until the age of 3 months
4. Neuro-motor and developmental outcome during the first 2 years corrected age

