### **Statistical analysis**

Results are presented as mean  $\pm$  standard deviation. We will compare the results of infants treated with insulin to those receiving standard care on an intention to treat basis and within each group we will also compare the results of SGA infants to AGA infants.

Comparison between the groups on all different time points will be analysed using the unpaired t-test.

Within group differences between different time points and differences between the groups in the changes of the values in time will be analysed with repeated measures analysis of variance (ANOVA).

A p value of  $<0.05$  will be considered as statistically significant

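### The protocol contradicts itself on which outcomes are primary, names no primary variable or visit, and tests every visit at an unadjusted p<0.05

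*Protocol*

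**What the plan says.** Four places in the protocol rank the outcomes of the local study.

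- **Summary of the local amendment, primary efficacy variable:** "Improved growth, body composition, neuro-motor development and function of the neuro-endocrine axes".
- **Primary questions:** the first asks "Does insulin replacement in preterm infants during the first week of life improve insulin sensitivity, early postnatal growth, catch up growth and body composition". The second asks whether treatment would "have implications for the development and function of the HPA and HPG axis", and the third whether it would "have implications for the neuro-motor development during infancy and early childhood".
- **Objectives, Primary:** a single item, "Growth and catch up growth and body composition during the first two years corrected age".
- **Objectives, Secondary:** insulin sensitivity, adrenal function, the HPG axis and "Neuro-motor and developmental outcome during the first 2 years corrected age".

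The Statistical analysis section fixes the tests: "Comparison between the groups on all different time points will be analysed using the unpaired t-test". It adds a repeated measures ANOVA for within-group change and for between-group differences in change over time, and comparisons of SGA with AGA infants within each arm. It sets p<0.05 as the threshold for significance. Sample size consideration bases the 30 evaluable infants per group on a difference of 0.5 SDS in growth parameters, without saying which parameter or which visit.

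**The concern.** Insulin sensitivity, the HPA and HPG axes and neuro-motor development are primary in one part of the protocol and secondary in another. A report could follow either part and claim to follow the protocol, so the same data would support different primary conclusions.

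Even under the narrower Objectives, the primary outcome is a domain and not a variable. It covers many measurements over two years, each compared between arms at each visit at p<0.05. Any one significant variable-by-visit result could be presented as the primary finding, and the 5% error rate that the sample size assumes would not apply to that claim.

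**Working it through.** **Step 1. The passages side by side**

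| Outcome | Summary of the local amendment | Primary questions | Objectives |
|---|---|---|---|
| Growth, body composition | primary | primary | primary |
| Neuro-motor development | primary | primary | secondary |
| HPA and HPG axes | primary (as neuro-endocrine axes) | primary | secondary |
| Insulin sensitivity | not named | primary | secondary |

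The Summary and the Primary questions differ in substance only on insulin sensitivity. The contradiction is between those two and the Objectives. The sample size rests on growth, which agrees with the Objectives.

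**Step 2. Number of tests**

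- Visits, from Measurement of outcomes amendment: day 7, 32 weeks, term, and 3, 6, 12 and 24 months = 7.
- Variables, same section: at least 3 (weight, crown-heel length, head circumference). There are about 10 when total length, chest circumference, total circumference and four skin-fold sites are added. The 10 is a count made for this review, not a figure in the protocol.
- Tests: 1 × 7 = 7, 3 × 7 = 21, 10 × 7 = 70.

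**Step 3. Upper reference, independent tests**

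The plan's own error rate is 5%, which holds for one test. For k independent tests with no true effect, the chance of at least one p<0.05 is 1 − 0.95^k:

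- k = 7: 1 − 0.95^7 = 30.2%
- k = 21: 1 − 0.95^21 = 65.9%
- k = 70: 1 − 0.95^70 = 97.2%

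**Step 4. Correlated tests**

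Measurements on one infant are correlated, so the true figures are lower. The protocol gives no correlations. Assumed here: 0.5–0.8 between variables and 0.7–0.9 between adjacent visits, falling off with distance in time. Null trials with 30 infants per arm were simulated, with an unpaired two-sided t-test on every variable at every visit.

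| Growth variables × 7 visits | Tests | Chance of at least one p<0.05 |
|---|---|---|
| 1 | 7 | about 14–22% |
| 3 | 21 | about 28–48% |
| about 10 | 70 | about 42–82% |

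The higher figure in each row goes with the weaker correlation.

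**Step 5. The broad primary set**

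To the 21 growth tests add:

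- HPG axis: 3 urine measures at 5 times = 15
- DHEAS in plasma and saliva at 2 visits = 4
- cortisol = 1
- HOMA at 2 visits = 2
- developmental measures, assumed = 8

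The total is 21 + 15 + 4 + 1 + 2 + 8 = 51 tests. A separate simulation assumed equal correlation of 0.5–0.9 between visits, 0.5–0.8 between growth variables and none between domains. It gave 62–83%.

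**Step 6. After the fix**

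One variable with one primary test has a type I error of 5%. Keeping three variables at seven visits as co-primary under Bonferroni would need 0.05/21 = 0.0024 per test.

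**The case against.** **The document shows which version is operative.** The sample size is in growth SDS, which matches the Objectives. This stands, and it gives the direction of the fix. It does not remove the contradiction, because the field labelled primary efficacy variable and the Primary questions still say otherwise.

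**There are three incompatible definitions.** A reader might infer this from the three headings. The documents do not support it: HPA and HPG are the neuro-endocrine axes of the Summary, so there are in essence two versions. Mortality, the primary outcome of the multicentre trial, is not a further version and is unaffected.

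**The plan already has a longitudinal test.** The repeated measures ANOVA compares change over time between arms and suits an objective that covers two years. This is a fair point, and the t-tests are not the whole plan. But the ANOVA is not named as the primary test, and the t-tests do not depend on its result, so it does not control the error.

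**The inflation may be modest.** For three growth variables it stays below one half. It would be smaller still if only results favouring insulin counted: 11–26% for 21 tests in the simulation with equal between-visit correlation. This limits the claim about size, but the error is not held at the nominal level.

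**A statistical analysis plan could adjust for multiplicity.** It could, and the lack of an adjustment method alone would be no finding. However, which outcome is primary is stated in the protocol, in conflicting terms, and any correction would have to override the explicit testing rule.

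**Conclusion.** The concern holds. The protocol gives two conflicting sets of primary outcomes, neither of which fixes a variable and a time point, and it attaches an unadjusted p<0.05 to every visit. For growth alone, the chance of a false-positive result is roughly three to four times the nominal 5% for one variable (14–22%). It is 28–48% for three variables and 42–82% for about ten. These ranges rest on the assumed correlations and on the count of ten variables. The contradiction itself rests on no assumption.

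Two stronger readings are tempting but not supported:

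- **A false-positive primary result is more likely than not under every definition.** That is shown for the broad set (62–83% for about 51 tests), but not for the Objectives' version when three growth variables are counted.
- **Growth and body composition amount to 16 variables and 112 tests.** That count splits limb measurements which the protocol groups as total length and total circumference.

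**What to change.** 1. Make the Summary of the local amendment and the Primary questions agree with the Objectives and with the growth-based sample size. Insulin sensitivity, the HPA and HPG axes and neuro-motor development become secondary throughout.
2. Before any unblinded analysis, have the investigators name one primary growth variable on the SDS scale and one primary between-group test at two-sided 0.05. The test may be at a single visit, such as 24 months corrected age, or may be the group-by-time comparison already planned. Weight SDS at 24 months is one candidate, but no section singles it out and the choice belongs to the investigators.
3. Amend the Statistical analysis section so that all other variables and visits, and the SGA versus AGA comparisons, are secondary. They should be either adjusted for multiplicity within a domain or reported as estimates with 95% confidence intervals and no claim of significance.

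The change itself is protocol wording. Its price is that significant results in other domains, in body composition measures or at other visits can no longer be claimed as primary. Body composition in particular leaves the primary outcome, and the amendment should say so openly. Naming one variable will also oblige the investigators to state the standard deviation behind 30 per group. If it were 1 SDS, which is an assumption, power for a 0.5 SDS difference would be about 48%. That is a separate issue, but it will surface with this change.

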## Abbreviations

|       |                                            |
|-------|--------------------------------------------|
| ACTH  | adrenocorticotrophic hormone               |
| AGA   | appropriate for gestational age            |
| CRH   | corticotrophin releasing hormone           |
| DEXA  | dual energy x-ray absorptiometry           |
| FSH   | follicle stimulating hormone               |
| GA    | gestational age                            |
| GH    | growth hormone                             |
| GH-BP | GH-binding protein                         |
| HPA   | hypothalamic-pituitary-adrenal             |
| HPG   | hypothalamic-pituitary-gonadal             |
| IGF   | insulin-like growth factor                 |
| IGFBP | insulin-like growth factor-binding protein |
| IUGR  | intrauterine growth retardation            |
| LBW   | low birth weight                           |
| LH    | luteinizing hormone                        |
| SGA   | small for gestational age                  |
| SDS   | standard deviation score                   |
| VLBW  | very low birth weight                      |

## Introduction

It is well recognized that disturbances to the fetal-maternal environment resulting in a transient restraint of prenatal growth can influence and even undermine our state of health well into adulthood. This led to the development of the fetal origins of adult disease paradigm, which resulted in a refocusing of research efforts to investigate the lifelong consequences of perinatal influences on chronic diseases and the function of neuro-endocrine axes. Meanwhile, during the last decade an abundance of data on the short- and long-term diseases associated with intrauterine growth retardation (IUGR) were published. The association between IUGR and cardiovascular disease and its risk factors (hypertension, insulin resistance) caused by the fetal adaptations to the limited supply of nutrients that lead to permanent changes in structure and metabolism (programming) is nowadays well established [1-8]. In addition, growing evidence has been documented on the relationship between IUGR and an increased risk of short stature, premature adrenarche, early puberty, polycystic ovary syndrome and associated fertility problems [9-11] suggesting that the natural history of growth, adrenal and sexual physiology may originate in the very early development, even in intrauterine life [12].

One may argue whether preterm born children may as well be predisposed to the same risks observed in children born at term after IUGR since they also go through a period of restricted growth and stress, but instead of intrauterine, like in at term born small for gestational age (SGA) children, this takes place after birth in the extra-uterine environment during a postnatal period corresponding to the last trimester. It is plausible that in this period adaptations are made that are comparable to the fetal adaptations during IUGR. These postnatal adaptations can also be the origins of disease in later life e.g. poor childhood growth, reduced insulin sensitivity in childhood, disturbances in the development and function of the hypothalamic pituitary gonadal axis (HPG-axis) and the hypothalamic-pituitary-adrenal axis (HPA-axis) and a higher risk to develop the metabolic syndrome in later life.

Our intervention, continuous insulin replacement in the first week of life (NIRTURE study) aims to improve anabolism and insulin sensitivity which may

prevent the adaptations that lead to permanent changes in organ-structure and metabolism eventually responsible for chronic diseases in adult life.

## **Rationale**

At birth the disruption of the placental supply of nutrients leads to a period of catabolism. In term born infants usually the weight loss is maximal two or three days after birth and birth weight is recovered after seven days. In very low birth weight infants (<1500g) this period of catabolism is much more prolonged and birth weight is often not regained for several weeks. VLBW infants have a high incidence of hyperglycaemia, caused by a combination of insulin resistance and relative insulin deficiency.

There is increasing evidence that not only the prenatal period but also the early postnatal period is critical for pancreatic development. At this time a complex set of signals appears to influence pancreatic development and  $\beta$  cell survival. This has implications both in terms of acute glucose control but also relative insulin deficiency is likely to play a role in poor postnatal growth, which has been associated with later motor and cognitive impairment, and fewer  $\beta$  cells are linked to risk of type 2 diabetes later in life.

Recent studies show that changes in metabolic and endocrine processes because of a period of catabolism pre- or postnatally are not only profound in the early postnatal period but also linked to chronic diseases in later life. Infants born either prematurely or SGA because of IUGR are at increased risk of poor childhood growth and reduced insulin sensitivity in childhood also leading to a higher risk of the metabolic syndrome in later life [13-17]. With respect to this, it is important to mention that the underlying mechanisms leading to poor childhood growth and reduced insulin sensitivity are far from clear. There are indications that especially SGA born prepubertal children who did catch up in height and/or weight during the first years of life, i.e. not showing a poor childhood growth, have a reduced insulin sensitivity [13].

One can imagine, that during the postnatal period and even during childhood there are not only disturbances in growth but there may also be disturbances in body composition. Cooke et al. [19] investigating body composition during the

first year of life in preterms and infants born at term did not found differences in body composition between the groups despite the preterms studied were smaller. Also Bolt et al. [18] in an observational cohort study of preterms did, however, not observe differences in body composition relative to body weight between AGA and SGA infants during the first year of life, despite differences in catch up growth.

Our intervention aims to improve anabolism and insulin sensitivity during the first week of life. As early growth is increasingly being shown to be important in terms of long-term metabolism [20-23], it is important that we review these children in early childhood to assess their growth, body composition and insulin sensitivity.

In extremely preterm infants and SGA infants born at term Growth Hormone (GH) resistance is found. These infants have higher levels of GH and insulin-like growth factor binding protein-1 (IGFBP-1) and low levels of insulin-like growth factor-1 (IGF-1) and IGFBP-3. Both IGF-1 and IGFBP-3 are positively related to growth. Low levels might be one of the causes of the slow postnatal growth in VLBW infants.

Levels of IGF-1 and the inhibitory IGF binding protein IGFBP-1 and IGFBP-3 are regulated by insulin in the newborn [24-26]. Insulin stimulates IGF-1 and IGFBP-3 synthesis and inhibits IGFBP-1 synthesis [27]. It is well established that preterm infants are at high risk of developmental delay and early growth has also been linked to neuro-developmental outcome. IGF-I has an important role in fetal and postnatal brain growth [27-28]. Furthermore, low IGF-1 levels have been implicated in the pathogenesis of retinopathy of prematurity [29-31]. Thus theoretically, improved insulin delivery and restoration of IGF-I levels could have important implications for the long-term outcome as well as the short-term growth of very low birth weight babies.

In early life there are differences in the development and function of the HPA-axis between preterm and term born infants and between AGA and SGA preterm infants. During gestation the HPA-axis develops and in the third trimester of gestation this axis fully matures. The adrenal cortex function in preterm infants is

closely related to the duration of gestation. Bolt et al. showed that AGA preterms born < 30 weeks of gestation had a lower response of cortisol to ACTH stimulation on the 5th to 10th day of life compared to AGA preterms born between 30 and 33 weeks [32]. In preterm infants birth weight SD score as a measure for intrauterine growth was positively associated with the cortisol response to ACTH stimulation [33]. The lower adrenal response to stimulation may be involved in the higher risk of neonatal morbidity in very preterm infants, and especially in growth restricted preterm infants. In agreement with this, Scott et al. found that plasma cortisol levels in preterm infants not only significantly correlated with gestational age but also with markers of illness [34].

In conclusion, prematurity and fetal growth restriction have consequences for the function of the HPA-axis in the neonatal period and this is probably associated with neonatal morbidity.

With respect to morbidity in adult life one of the proposed mechanisms underlying the associations between intrauterine growth restriction and adult cardiovascular disease and its risk factors (hypertension, insulin resistance) is intrauterine programming of the HPA-axis. Phillips et al. found an inverse relation between birth weight and fasting plasma cortisol in adults. These cortisol concentrations correlated positively to systolic blood pressure, fasting and 2-hour plasma glucose concentrations after an oral glucose tolerance test, plasma triglyceride levels and insulin resistance [35,36]. Even in prepubertal SGA children born at term compared to AGA children born at term salivary cortisol concentrations during the day were higher, and therefore indicative of increased HPA-activity [37].

Case control studies comparing small for gestational age to normal birth weight children born at term show that in contrast to the low DHEAS levels at birth, DHEAS levels are higher than average in older low-birth weight children [10,13,38,39]. Recently, a large birth cohort study of unselected UK subjects (ALSPAC) showed a rather continuous inverse relationship between birth weight and DHEAS levels throughout the range of birth weights [40], comparable to the relationships between birth weight and disease risk in adulthood [41].

The increase in DHEAS levels seems to follow the typical pattern of rapid early postnatal weight gain that is seen in the majority of low birth weight children. There are also studies indicating that increased adrenal androgen secretion during childhood may be programmed by the combination of reduced fetal growth and rapid early postnatal weight gain [42]. In particular the rapid weight gain during the first 3 years of life appears to influence the onset of adrenarche [43], suggesting that DHEAS could be regulated by weight gain. Precocious or premature adrenarche refers to an early increase in adrenal androgen production secondary to an early isolated maturation of the adrenal gland [44-49]. Premature adrenarche generally occurs with increasing frequency between the ages of 3 and 8 yr, although it may present as early as 6 months of age [50]. IGF-1 and insulin levels are higher in children with premature adrenarche than in control children [50-52], and might therefore link the combination of low birth weight and rapid infancy weight gain to the development of higher adrenal androgen production in later life [9,10,13,53]. Clinical features of adrenal hyperandrogenism are associated with adverse effects on body composition, insulin resistance, and increased risk of future progression to ovarian hyperandrogenism in the early years post-menarche.

Premature born children also go through a period of restricted growth and stress; it is plausible that the adaptations made in this early neonatal period can also be the origins of adrenal hyperandrogenism and future diseases in later life.

Puberty, defined as the achievement of interactions between the neuro-endocrine unit, the gonads and the hypothalamic-pituitary-gonadal (HPG)-axis, has its origin in the fetal period, when this endocrine system is already active. This endocrine unit becomes suppressed during infancy (3-6 months after birth) and is reactivated at the onset of puberty.

Over the last decade, growing evidence has also been documented on the relationship between IUGR in term born children and pubertal development, indicating changes in timing and progression of puberty [9,54,55]. Both the role of IUGR and the mechanisms behind the onset and progression of puberty are still elusive. Based on the knowledge that the HPG-apparatus in the human fetus is functional by 50 days of gestation, one can postulate that the maturational

process of this endocrine system that progresses even until 3 to 6 months after birth can be influenced in periods of restricted growth both in-utero and ex-utero. As premature born children also go through a period of restricted growth and stress, it is plausible that prematurity has also consequences for the development of the HPG-axis and later puberty.

